#### 4.4 Sample size calculation

We based our sample size calculation on a superiority design. As stated before the EQ-5D will serve as primary outcome measure. We have used the results from earlier studies on this subject for our sample size calculation(17–19). For the sample size calculation, we hypothesized that the EQ-5D will be higher in the PLA group. Using a two-sided significance level ( $\alpha$ ) of 0.05 and a power ( $\beta$ ) of 80% with a standard deviation (SD) of 0.3 and a minimal clinical important difference (MCID) of 0.08 (derived from the study mentioned before) a total of 222 subjects are needed in each treatment arm. Taking into account a 25% loss to follow-up after six months, a total number of 610 participants are needed in this superiority design.

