## **6. METHODS**

### **6.1 Study parameters/endpoints**

#### **6.1.1 Main study parameter/endpoint**

The primary outcome is the patient (or proxy)-rated quality of life (EQ-5D-5L) at 6 months after surgery.

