### **Baseline assessment**

At baseline we will assess the EQ-5D-5L, the ADL functionality (KATZ), pre-mobility score and the living status using the Dutch Hip Fracture Audit (DHFA) registration. The assessment of the above outcomes is based on the health status prior to the trauma.

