**8.1 Primary study parameter(s)**

In the primary GEE model, the primary outcome variable studied (health related quality of life on EQ-5D) will be analyzed as a dependent variable, using treatment allocation (DLA vs. PLA) as between subjects' variable and time as within subjects' variable. In a similar way, continuous secondary outcome variables will be analyzed using similar GEE models. All models will assess the interaction term of group and time, to evaluate whether the change over time differed between PLA and DLA.

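### Section 8.1 names only the group-by-time interaction for the primary GEE and does not fix the 6-month PLA–DLA difference on which the endpoint and the 80% power rest

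*Protocol*

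**What the plan says.** Section 6.1.1 defines the endpoint at a single time point: "The primary outcome is the patient (or proxy)-rated quality of life (EQ-5D-5L) at 6 months after surgery". Section 4.4 hypothesises a higher EQ-5D level under PLA and sizes the trial "with a standard deviation (SD) of 0.3 and a minimal clinical important difference (MCID) of 0.08", two-sided 5% significance and 80% power. It concludes that "a total of 222 subjects are needed in each treatment arm".

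Section 8.1 makes EQ-5D the dependent variable of a GEE with allocation between subjects and time within subjects. It then says: "All models will assess the interaction term of group and time, to evaluate whether the change over time differed between PLA and DLA". No contrast at 6 months is named in section 8, 8.1 or 8.2. Section 8.1 does not call the interaction the sole or confirmatory test, and it does not say whether baseline is one of the time levels.

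Under section 6.4 (Follow-up data collection), EQ-5D-5L is collected at baseline, 3 and 6 months. On the baseline value, section 6.4 (Baseline assessment) says: "The assessment of the above outcomes is based on the health status prior to the trauma". It is collected after the fracture, so it is a recalled score.

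**The concern.** Endpoint and sample size both refer to a difference in level at 6 months. The one effect that the analysis section names is a difference in change over time. A GEE with group, time and their interaction yields several p-values: the interaction, the group term (whose meaning depends on coding and on the time levels) and any visit-specific contrast. If none is designated, the primary result can be chosen after the data are seen. That matters more here because section 6.2 states that surgeons, patients and outcome assessors cannot be blinded.

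The power statement is also affected. The 80% was calculated for one contrast, and the power of the interaction depends on quantities that section 4.4 does not contain: the correlation between visits, the size of the effect at 3 months, and whether baseline is a time level. The correlation is especially uncertain because the baseline is a recalled pre-fracture score.

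**Working it through.** **Inputs from the protocol.** Two-sided α 0.05, power 80%, σ = 0.3, δ = 0.08, n = 222 per arm, 25% loss, total 610 (section 4.4); 1:1 allocation and EQ-5D at baseline, 3 and 6 months (section 6.4).

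**Assumptions, because the protocol gives no figure.** Correlation ρ between any two visits from 0.2 to 0.7; the same SD at each visit; no expected baseline difference (randomised patients); no clustering.

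**Step 1: reproduce the plan's figure.** n = 2σ²(1.960 + 0.842)²/δ² = 2 × 0.09 × 7.849/0.0064 = 220.7, i.e. 221 per arm. The t-test version gives 221.7, i.e. 222. Power at 222: SE = 0.3 × √(2/222) = 0.0285; 0.08/SE = 2.81; 2.81 − 1.96 = 0.85; power 80.2%. For loss, 444/0.75 = 592, against 610 stated. Taking 610 less 25% leaves 228.75 per arm and 81.4% power. The 222 is thus a two-group comparison of means at one time point, with no baseline or repeated-measures term.

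**Step 2: change from baseline to 6 months (1 df).** Expected value 0.08 − 0 = 0.08, as for the 6-month difference. The SD becomes σ√(2(1 − ρ)), which equals σ only at ρ = 0.5.

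**Step 3: joint interaction over three visits (2 df).** With effects δ₃ at 3 months and δ₆ = 0.08 at 6 months, the non-centrality is λ = [n/(2σ²(1 − ρ))] × (2/3)(δ₃² − δ₃δ₆ + δ₆²), and n/(2σ²) = 222/0.18 = 1233.3.
- δ₃ = 0 or 0.08: (2/3) × 0.0064 = 0.004267, so λ = 5.26/(1 − ρ).
- δ₃ = 0.04: (2/3) × 0.0048 = 0.0032, so λ = 3.95/(1 − ρ).

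Power is the probability that a non-central chi-square with 2 df exceeds 5.99.

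**Step 4: 6-month difference adjusted for baseline.** Expected value 0.08; SD σ√(1 − ρ²). Its variance relative to the change contrast is (1 − ρ²)/(2(1 − ρ)) = (1 + ρ)/2, below 1 for every ρ under 1.

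| ρ (assumed) | Change contrast, power | n per arm for 80%, change contrast | 2-df interaction, δ₃ = 0 or 0.08 | 2-df interaction, δ₃ = 0.04 | Baseline-adjusted 6-month difference |
|---|---|---|---|---|---|
| 0.2 | 60.3% | 354 | 62.6% | 49.8% | 81.8% |
| 0.3 | 66.1% | 310 | 68.9% | 55.6% | 83.8% |
| 0.4 | 72.7% | 265 | 75.9% | 62.6% | 86.6% |
| 0.5 | 80.2% | 221 | 83.6% | 71.1% | 90.0% |
| 0.6 | 88.1% | 177 | 91.1% | 81.0% | 94.0% |
| 0.7 | 95.2% | 133 | 97.1% | 91.1% | 97.6% |

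Equal correlations are a simplification. If the two follow-up visits correlate at 0.7 and only the correlation with baseline varies from 0.2 to 0.7, the 2-df power is 94% to 97% for δ₃ = 0, 61% to 91% for δ₃ = 0.04, and 54% to 97% for δ₃ = 0.08.

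**Step 5: baseline not a time level.** The interaction is then δ₆ − δ₃. A constant benefit of 0.08 at both visits gives 0.08 − 0.08 = 0, and the test rejects at its 5% significance level only.

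**The case against.** The strongest reply is that section 8.1 says only that the interaction will be assessed. Section 8 gives the purpose of the GEE as the effect of surgical approach, section 6.1.1 fixes the time point, and a model with group, time and interaction delivers the 6-month difference directly. A reader might infer that the interaction replaces the 6-month comparison and is the confirmatory test. The text does not support that. What stands is that the contrast carrying the primary conclusion is not named, while a different effect is.

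A second reply is that contrasts and the handling of baseline are often left to the SAP, which is not at hand. That would answer mere silence, but section 8.1 states which term all models assess and why. A SAP that followed it would carry the mismatch forward, and one that named the 6-month contrast as primary would have to go beyond the protocol's wording.

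Third, among randomised patients the expected baseline difference is zero, so the 1-df change contrast has the same expected value as the 6-month difference. It is tempting to say that the analysis answers a different question. For that contrast in the RCT it does not, and only precision differs. This reassurance does not cover the joint 2-df test or the non-randomised natural experiment of section 6.3.

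Fourth, the 5% result needs baseline to be left out of the time factor. With EQ-5D collected at baseline and the stated interest in change over time, that is the less likely reading. It shows what the wording leaves open and is not a description of the plan.

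Finally, leaving baseline out as a covariate is not an error in itself. Adjustment belongs to the remedy.

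**Conclusion.** The point holds as an unfixed and mismatched primary contrast. Endpoint and sample size concern the 6-month difference, and the only effect named for the primary model is the group-by-time interaction. The stated 80% (80.2% recomputed) belongs to the former and does not automatically apply to the latter.

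A reader might conclude that the trial is underpowered. The documents do not show that. The 1-df change contrast falls below 80% for ρ under 0.5, equals it at 0.5 and exceeds it above. With equal correlations the 2-df interaction has 50% to 91% power if the 3-month effect is 0.04, and 63% to 97% if it is 0 or 0.08. All these ranges rest on assumed correlations, a common SD of 0.3 and no clustering. The mismatch itself rests on the text of sections 4.4, 6.1.1 and 8.1 and on the reproduction of 222 per arm, and needs none of those assumptions.

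**What to change.** For the primary outcome, replace the last sentence of section 8.1 with wording to this effect: EQ-5D-5L at 3 and 6 months are the repeated outcomes; the model contains group, time, group-by-time and baseline EQ-5D-5L as a covariate; the single primary test is the model-based PLA–DLA difference at 6 months with its 95% CI; the interaction and the 3-month contrast are supportive.

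This ties the analysis to sections 6.1.1 and 4.4. Section 4.4 can stay as it is, since the unadjusted calculation is then conservative with respect to baseline adjustment. The cost is a wording change in section 8.1, carried into the SAP, with no new data, visits or patients. It should be made before outcome data are examined by arm.

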**8.2 Secondary study parameter(s)**

Dichotomous secondary outcome measures will be analyzed using chi square statistics and logistic regression models. Subgroup analysis will be performed for patients with dementia. For all analyses, a two-tailed value of  $p < 0.05$  is considered to be significant.

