#### **6.1.2 Secondary study parameters/endpoints**

Secondary outcomes are: ADL functionality (KATZ), Balance test (SPPB), Tendency to Fall (FES-I), Numbers of falls, additional injuries as a result of falling, Pain (NRS), Re-interventions, Mobility (pre-fracture mobility score), Discharge destination, (surgical) complications and cost-effectiveness.

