### **Follow-up data collection**

The baseline and follow-up assessment will be conducted by the coordinating research team of the OLVG. There are three follow-up moments at 4 weeks, 3 and 6 months postoperative. The primary outcome measurement EQ-5D-5L and the secondary outcomes FES-I scale will be assessed through questionnaires online, by hardcopy or by phone at baseline, 3 and 6 months postoperatively. The health care utilization questionnaire will be assessed at 4 weeks, 3 and 6 months follow-up. The questionnaires will be handed out by the coordinating researcher. Other secondary outcome measurements (e.g. KATZ, mobility score, complications, re-operations) are detailed in the DHFA at baseline and 3 months post-operatively and will be assessed through questionnaires online, by hardcopy or by phone at 6 months after surgery and will be handed out by the coordinating researcher.

The assessment of the Short Physical Performance Battery (SPPB) balance test, which is not included in the DHFA, will be performed by one of the study researchers or nurse practitioner to protect continuity and feasibility and will only be assessed in patients included in the RCT. The SPPB will not be assessed in all patients, but in a subgroup of the patient population because the sample size is smaller. The SPPB is a group of measures that combines the results of the gait speed, chair stand and balance tests.(24)

The follow-up questionnaires will contain:

- Health-related quality of life as measured by the EQ-5D questionnaire. The EQ-5D-5L is a descriptive system of health-related quality of life states consisting of five dimensions (mobility, self-care, usual activities, pain/discomfort and anxiety/depression)(25).
- The Katz Index of Independence in Activities of Daily Living, the Katz ADL, is an instrument to assess functional status as a measurement of the client's ability to perform activities of daily living independently consisting six functions (bathing, dressing, toileting, transferring, continence and feeding)(26).
- The Falls Efficacy Scale-International (FES-I) is a short, easy to administer tool that measures the level of concern about falling during social and physical activities inside and outside the home whether or not the person actually does the activity(27).
- Additionally injuries as a result of falling and other (indication to) re-interventions

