## **6.5 Withdrawal of individual subjects**

Subjects can leave the study at any time for any reason if they wish to do so without any consequences. The investigator can decide to withdraw a subject from the study for medical or other reasons. Data collected prior to individual subject withdrawal will be used for data analysis, unless the patient requests otherwise.

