## **6.6 Replacement of individual subjects after withdrawal**

We do not intend to replace individual subjects after withdrawal, as we anticipated a 25% of lost to follow-up. If the drop-out rate appears to exceed this estimation, we will reconsider.

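### Re-interventions and surgical complications accrue over 6 months with 25% planned loss, but section 8.2 analyses them only as yes/no, which may bias absolute risks

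*Protocol*

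**What the plan says.** Section 8.2 of the protocol gives one rule for all yes/no secondary outcomes: "Dichotomous secondary outcome measures will be analyzed using chi square statistics and logistic regression models". The secondary outcomes in section 6.1.2 include "Re-interventions, Mobility (pre-fracture mobility score), Discharge destination, (surgical) complications and cost-effectiveness".

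On follow-up, section 4.4 reads "Taking into account a 25% loss to follow-up after six months, a total number of 610 participants are needed in this superiority design". Section 6.6 plans no replacement of subjects who withdraw, "as we anticipated a 25% of lost to follow-up". Section 6.5 adds: "Data collected prior to individual subject withdrawal will be used for data analysis, unless the patient requests otherwise".

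On data sources, section 6.4 (Follow-up data collection) says: "Other secondary outcome measurements (e.g. KATZ, mobility score, complications, re-operations) are detailed in the DHFA at baseline and 3 months post-operatively". The 6-month values of the same items come from study questionnaires.

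Continuous outcomes get longitudinal GEE models (section 8.1). Multiple imputation is named only for the economic evaluation (section 8.3). Section 8 names no time-to-event method and does not say how a patient who dies is counted for these events.

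**The concern.** Chi-square and logistic regression need one status per patient over a common window. A patient who has a re-intervention and is then lost has a known status. A patient lost event-free before 6 months does not, and a binary analysis has no way to use the event-free time that was observed. GEE does use partial data for the continuous outcomes, so the gap concerns the event outcomes only.

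These two outcomes carry much of the harm side of the comparison. Section 1 says that the presumed benefit of the posterolateral approach may be offset by more dislocations, and section 2 names re-interventions and complications in a secondary objective. Readers will set their absolute risks beside the EQ-5D result. Section 6.2 rules out blinding of patients and assessors, so unequal loss between arms cannot be excluded.

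**Working it through.** **The plan's own figures.** With SD 0.3, difference 0.08, two-sided 5% and 80% power (section 4.4), n = 2 × (1.960 + 0.842)² × 0.3² / 0.08² = 221 per arm; the t-based version gives 221.7, so 222. Then 444 / 0.75 = 592. The stated 610 is slightly larger and corresponds to 1 − 444/610 = 27.2% loss. A loss of 25% of 610 is about 152 patients. The plan states no event rate for any yes/no outcome.

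**Assumptions, none of them in the protocol.** True 6-month risks are p = 10% and 5% (difference 5.0 points, odds ratio 2.11). Events and losses are spread evenly over 6 months and are independent. A fraction d is lost. Power uses all 610 patients as two arms of 305.

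A lost patient who would have had an event has it before loss half of the time. Observed events are therefore (1 − d)p + dp/2 = (1 − d/2)p. With d = 0.25 this is 0.875p.

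**Equal loss of 25%:**

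| Handling of lost patients | Risks | Difference | Odds ratio |
|---|---|---|---|
| All counted as event-free unless an event was seen | 8.75% v 4.38% | 4.4 points | 2.10 |
| Event-free lost patients excluded, earlier events kept | 0.0875/0.7625 = 11.5% v 0.04375/0.75625 = 5.8% | 5.7 points | 2.11 |
| All lost patients excluded | 10% v 5% | 5.0 points | 2.11 |

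Row 1 is 12.5% too low in each arm. Row 2 is about 15% too high. In row 2 the patients without an event are (1 − d)(1 − p), so each arm's odds are multiplied by (1 − d/2)/(1 − d), which cancels from the odds ratio when d is the same in both arms. Row 3 is unbiased under these assumptions but discards events already observed. Chi-square power is 65% with complete data, 59% under row 1, and 53% under row 3 (229 per arm).

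**Unequal loss, 30% v 20% in either direction.** Row 1 handling gives odds ratios of 1.97 and 2.23. Row 2 handling gives 2.28 and 1.96.

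**No true difference, 6% in both arms, loss 20% v 30%.** Row 1 handling gives 5.4% v 5.1%. Row 2 handling gives 0.054/0.806 = 6.7% v 0.051/0.709 = 7.2%. The standard error of the difference is √(2 × 0.06 × 0.94 / 305) = 1.9 points, so these spurious gaps of 0.3 and 0.5 points are about 0.16 and 0.26 of a standard error.

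**Effect of the registry.** Suppose the DHFA captures every event to 3 months, including those in patients lost to the study. Half of the 25% are lost before 3 months and then miss half of their events; the other half miss a quarter on average. The shortfall is 0.125 × 0.5 + 0.125 × 0.25 = 9.4% of p, instead of 12.5%. It is smaller still if events cluster early. The overstatement in row 2 does not shrink this way: if event-free lost patients are still excluded, 10% becomes 0.0906/0.7656 = 11.8%.

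**The case against.** Section 8.2 names a family of methods and no coding of lost patients. A reader might infer that event-free patients lost early must be either miscoded or dropped. The text does not force that. Logistic regression can be run on complete cases, on imputed or weighted data, or on a 3-month window, and those details may properly sit in a statistical analysis plan. Section 6.5 keeps earlier data in general terms and does not require keeping events while excluding event-free patients.

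A reader might also extend the point to every yes/no outcome. That fails: discharge destination is settled at discharge, and a status recorded at a visit is not a censored event time.

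The 25% was set for the EQ-5D sample size. A patient who stops answering questionnaires is not thereby lost to the registry before 3 months. The protocol does not say whether the 25% includes deaths. A patient who dies event-free is correctly counted as without an event in a cumulative incidence, so any deaths within the 25% reduce the understatement.

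Finally, it is tempting to say that the comparison between arms is invalid. With equal loss it is not: the odds ratio is 2.10 to 2.11 against 2.11.

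All of this stands and limits the point. What remains is that the protocol does fix the method for these two outcomes, and that method by itself neither uses partial follow-up nor treats death as a competing event.

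**Conclusion.** The point holds for re-interventions and surgical complications only, as a minor improvement to secondary analyses. Under even, independent loss of 25%, each arm's 6-month risk may be about 13% too low or 15% too high, depending on a coding that the protocol does not state. With assumed risks of 10% and 5%, the risk difference moves from 5.0 to 4.4 or 5.7 points. Some power is also lost. The understatement is smaller to the extent that the registry captures events to 3 months or the 25% includes deaths. The odds ratio is materially affected only if loss differs by arm or is related to the event. All event rates and loss patterns here are assumptions, so the sizes are illustrative.

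**What to change.** In section 8.2, for re-interventions and surgical complications:

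- Analyse time from surgery to first event, censored at last contact or last registry check, with death as a competing event.
- Report the 6-month cumulative incidence per arm, with the difference and its 95% CI.
- In the randomised part only, compare arms with a centre-stratified cause-specific Cox model.
- In the natural experiment (section 6.3), centres use a single approach, so stratifying by centre leaves no contrast. Use a model that does not stratify by centre and that accounts for clustering.
- Keep logistic regression for outcomes with one fixed assessment time, such as discharge destination.

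The cost goes a little beyond wording. Event dates must be recorded, including for events first reported on the 6-month questionnaire; section 6.4 already gives the team access to the surgical report. Death dates must be recorded for participants: section 6.9 lists date of death, but for comparing included with missed patients, and does not show that it is linked to trial records. The analysis takes slightly more work. Censoring at last contact still assumes that loss is unrelated to the event, so the change does not cure event-related dropout.

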### Secondary Objectives:

- Does a hemiarthroplasty using the posterolateral approach lead to a reduction in health care related costs compared to the direct lateral surgical approach?
- Does a hemiarthroplasty using the posterolateral approach lead to better patient outcomes regarding: ADL functionality, balance, tendency to fall, pain, mobility, the number of re-interventions or complications and the discharge destination.

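### Section 8.2 calls every secondary and dementia-subgroup result below p = 0.05 significant, with no order, adjustment or exploratory status; the primary EQ-5D test is not affected

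*Protocol*

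**What the plan says.** Protocol section 6.1.1 names a single primary endpoint: "The primary outcome is the patient (or proxy)-rated quality of life (EQ-5D-5L) at 6 months after surgery".

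Section 6.1.2 then gives the secondary list. It opens "Secondary outcomes are: ADL functionality (KATZ), Balance test (SPPB), Tendency to Fall (FES-I), Numbers of falls, additional injuries as a result of falling", continues with pain, and ends "Re-interventions, Mobility (pre-fracture mobility score), Discharge destination, (surgical) complications and cost-effectiveness". Leaving cost-effectiveness aside, that makes ten clinical outcomes: KATZ, SPPB, FES-I, number of falls, fall injuries, pain, re-interventions, mobility, discharge destination and complications.

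Section 2 (Secondary Objectives) puts one directional question over most of these: "Does a hemiarthroplasty using the posterolateral approach lead to better patient outcomes regarding: ADL functionality, balance, tendency to fall, pain, mobility", followed by re-interventions, complications and discharge destination. That is eight of the ten; number of falls and fall injuries are not in it. The Summary also lists eight clinical secondary outcomes.

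Section 8.2 adds "Subgroup analysis will be performed for patients with dementia". The next sentence fixes the threshold: "For all analyses, a two-tailed value of" p < 0.05 "is considered to be significant".

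No section orders the secondary outcomes, names a key secondary, divides alpha, makes a secondary test conditional on the primary result, or calls secondary or subgroup results exploratory.

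**The concern.** The threshold in 8.2 is a rule about what counts as significant, and it applies to all analyses. Read with the directional objective in section 2, it lets any one of eight to ten outcomes, or the dementia subgroup, supply a result that the protocol itself calls significant, whatever happens to EQ-5D.

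This matters more than usual here because the Introduction describes effects that may run in opposite directions. The posterolateral approach is presumed to give faster rehabilitation and better balance, at the price of more dislocations. If EQ-5D shows no difference, an isolated small p-value for pain, fear of falling or the dementia subgroup could be presented under the plan as an established difference between the approaches. How often chance alone would produce such a result can be calculated.

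**Working it through.** **The plan's own figure.** The protocol gives no family-wise error rate for the secondary outcomes. Its only error-rate calculation is the sample size in section 4.4, for EQ-5D alone: two-sided alpha 0.05, power 80%, SD 0.3, difference 0.08.

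- Per arm: n = 2 × (1.960 + 0.842)² × (0.3/0.08)² ≈ 221 by the normal approximation. The t-based value is 221.7, rounded up to 222, which matches the stated 222. Power at 222 per arm is 80.2%.
- Total after 25% loss: 444/0.75 = 592. The protocol states 610, so the planned number is not short.

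Nothing in this calculation depends on the secondary outcomes, and the corrections proposed here leave it unchanged.

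**Chance of at least one false significant result.** Inputs: 0.05 two-sided per test (section 8.2); k = 8 (section 2) or k = 10 (section 6.1.2). Assumptions: one test per outcome and no true difference on any outcome. Under independence the chance is 1 − 0.95^k:

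- k = 8: 1 − 0.95^8 = 33.7%
- k = 10: 1 − 0.95^10 = 40.1%
- k = 11 (ten outcomes plus one subgroup test): 1 − 0.95^11 = 43.1%

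The expected number of false positives among ten tests is 10 × 0.05 = 0.5, whatever the correlation.

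**Correlated outcomes.** These outcomes are probably positively correlated. The protocol gives no correlations, so the values below are assumptions. The figures come from simulating 200,000 sets of equally correlated normal test statistics.

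| Assumed correlation | k = 8 | k = 10 | k = 10, at least one false result favouring the posterolateral approach |
|---|---|---|---|
| 0 | 33.7% | 40.2% | 22.4% |
| 0.3 | 29.9% | 35.0% | 17.7% |
| 0.5 | 25.0% | 28.7% | 14.3% |
| 0.7 | 19.1% | 21.3% | 10.6% |
| 0.9 | 11.9% | 12.7% | 6.4% |

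The one-direction figure under independence agrees with 1 − 0.975^10 = 22.4%.

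**If some differences are real.** Only true nulls can give false positives. If complications truly differ, nine nulls remain: 1 − 0.95^9 = 37.0%. If only five of the ten are true nulls: 1 − 0.95^5 = 22.6%. Both assume independence.

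**Further tests under the same rule.** The figures above count one test per outcome. Section 8 plans a per-protocol analysis beside intention-to-treat, section 8.1 a group-by-time term in all models, and section 8.2 both chi-square tests and logistic regression for dichotomous outcomes. Each gives further chances to cross 0.05. Their effect is not calculated here, because they are strongly related to tests already counted.

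**What full adjustment would cost.** A Bonferroni threshold for ten tests is 0.05/10 = 0.005. For a standardised effect of 0.08/0.3 = 0.267 with 222 per arm, power falls from 80% to about 50%.

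**The case against.** The strongest reply is that multiplicity among secondary outcomes is usually settled in the statistical analysis plan, which is not shown, and that the sentence in 8.2 only sets a nominal level and sidedness. Unadjusted secondary tests beside a single named primary are common practice. This has some force: a missing adjustment scheme alone would not be a finding. But the protocol is not silent. It attaches the word significant to every analysis that crosses 0.05, subgroup included, without qualification. An analysis plan could add an exploratory label, but the protocol sentence would then need to be read down to fit it.

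Several stronger readings are tempting but not supported:

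- **That the trial's main error rate is inflated, or that the secondaries rank with the primary.** They do not. There is one primary endpoint, a separate primary objective and a sample size built on it alone.
- **That all ten outcomes answer the patient-outcome objective.** Section 2 names eight.
- **That the true error is several times what the protocol promises.** The 0.05 is a per-test level; the protocol never states it as a family-wise rate for the secondaries.
- **That the trial sets out to change guidelines.** The protocol says that evidence is lacking and that generalizability will help implementation; it does not state guideline change as an aim.

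It is also fair that the count of tests depends on the reading. Sections 8.1 and 8.2 do not say how number of falls, discharge destination or the mobility scale will be classified, and the dementia analysis names neither an outcome nor an interaction test. The protocol's background also expects some real differences. These points change the exact percentage but do not remove the problem.

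Finally, forbidding any statement of significance on secondaries would go too far. It would also cover complications and re-interventions, where failing to notice a real harm matters too.

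**Conclusion.** The concern holds in limited form. Section 8.2 applies an unqualified significance rule to the ten clinical secondary outcomes and the dementia subgroup. With no true differences, the chance of at least one significant secondary result is about 34% for eight tests and 40% for ten under independence, and about 29% for ten at an assumed correlation of 0.5. For a false result in favour of the posterolateral approach among ten, it is about 14% at that correlation and 22% under independence. Stronger correlation lowers these figures, as the table shows.

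The figures rest on one test per outcome, all nulls true, and correlations that the protocol does not supply. The primary EQ-5D comparison, its 5% error and the sample size are unaffected. The point is of moderate weight: it limits what may be claimed from secondary and subgroup results and should be settled before the data are analysed.

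**What to change.** Amend section 8.2 as follows:

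1. Reserve the confirmatory two-sided p < 0.05 rule for the primary EQ-5D comparison at 6 months.
2. State that secondary and dementia-subgroup results are unadjusted and exploratory, and are reported as estimates with 95% confidence intervals. Nominal p-values may be shown. Harms such as complications and re-interventions are still reported in full.
3. If a confirmatory secondary claim is wanted, name one or two outcomes now and test them in a fixed order, each at 0.05, only after a significant primary result.

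This takes one or two sentences, needs no new data or patients, and costs the primary analysis no power. It also avoids the loss of power that full Bonferroni adjustment would bring. The price is that an isolated secondary p-value below 0.05 can no longer be presented as proof of a difference.
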